### Interventions

In consideration of the hardship in guaranteeing the quality of the decoction, we intend to use granules in this study. The conventional western medicine administration such as pyridostigmine, low-dose prednisone, and immunosuppressants is in the light of their prestudy treatment schedule. In order to avoid the effects of other Chinese herbs, any drug containing ingredients from Chinese herbs is not allowed except MBYD. Moreover, patients are not allowed to take antibiotics, probiotics, or anti-acids, which can obviously affect gut microbiota during the trial. For patients who develop an infection that requires antibiotics during the trials, they will suspend the cycle until symptoms resolve and antibiotics have been discontinued for 2 months, which is the time for the recovery of gut microbiota after antibiotics shown by the animal study [30]. After then, they will restart that cycle from the beginning.

The MBYD consists of *Astragalus Membranaceus* (*Huangqi*), *Radix Fici Simplicissimae* (*Wuzhimaotao*), *Rhizoma Atractylodis Macrocephalae* (*Baizhu*), *Radix Codonopsitis* (*Dangshen*)*, Poria Cocos* (*Fuling*), *Radix Bupleuri* (*Chaihu*), *Cimicifuga Foetida* (*Shengma*), *Pericarpium Citri Reticulatae* (*Chenpi*), *Angelica Sinensis* (*Danggui*), *Semen Coicis* (*Yiyiren*), *Rhizoma Dioscoreae* (*Shanyao*), *Radix Liquiritiae* (*Gancao*), and *Radix Scrophulariae* (*Xuanshen*). Patients with MG who have spleen *qi*-deficiency syndromes and kidney deficiency syndromes are usually diagnosed with spleen-kidney deficiency syndrome according to TCM theory and in that case, *Morinda officinalis* (*Bajitian*), *Cistanche Salsa* (*Roucongrong*), *Semen Cuscutae* (*Tusizi*), *Cornus Officinalis* (*Shanzhuyu*), *Taxillus sutchuenensis Danser* (*Sangjisheng*), and *Rosa laevigata Michx* (*Jinyingzi*), which are together used to replenish kidney *qi*, will be added in MBYD. Both the MBYD granules and the placebo granules were manufactured by Guangdong Yifang Pharmaceutical Co. Ltd.(10 g/bag, 2 bags three times a day, last number: J2004021). The placebo granules were identical to the MBYD granules in appearance, texture, color, and odor.

### Outcomes

Given the multi-component and multi-target characterization of TCM, an all-round assessment of its effective evaluation is significant. In this study, the primary outcome is the QMG score. The QMG score will be assessed by a physician with experience in MG according to the MGFA manual [29]. The QMG score has 13 items with 0–3 points for each item and a total score of 0–39 points. A higher QMG score indicates a more severe disease condition, and a decrease of 2.6 points is considered to be of clinical significance [31]. The secondary outcomes are the following:
TCM syndrome score. Assessing TCM syndrome score is based on “Diagnosis standards for common syndromes in traditional Chinese medicine” [32] issued by the Chinese Medicine Diagnostic Branch of China Association of Traditional Chinese Medicine. The measurement information of each symptom and sign of MG patient are weighted and summed according to the values of different symptoms and signs.The scores of the following scales: myasthenia gravis composite (MGC), myasthenia gravis activities of daily living profile (MG-ADL), myasthenia gravis quality of life (MG-QOL)The level of CD4+ Foxp3+ Treg cells and cytokines (IL-4, IL-17A, INF-γ, TGF-β) in the peripheral bloodThe alteration of gut microbiota. Before the trials begin and after each period, we will collect the patients’ fresh fecal samples and then immediately store them in the laboratory freezer at − 80 °C until analyses. We will analyze the gut microbiota in the stool samples in order to explore the mechanism of MBYD in MG therapy at the microbiological level by the 16S rRNA gene sequencing.The reduction and alleviation of side effects of western medicine for MG treatment

The safety assessments consist of the following items:
Laboratory tests, including serum alanine aminotransferase, aspartate aminotransferase, urea nitrogen, creatinine, and routine blood testsVital signs, physical examination, and electrocardiographAdverse events occurring during the study, including MG crisis, drug allergy, hepatorenal insufficiency, and other adverse drug reactions

The outcomes and the safety assessments will be conducted before the trials begin and at the end of each period.

### Sample size

We conducted the preliminary trials that 3 patients had finished all the three cycles. The mean and standard deviation (SD) of QMG scores (the primary outcome) difference between MBYD and placebo groups was (3.00±1.94). The sample size calculation was based on the effect of treatment with QMG scores [19]. We assumed that there were differences in treatment effect among different patients, and the difference value(Ψ) was 3.0. We used the two-sided test and set the type I error α of hypothesis test as 0.05 and the error β of class II as 0.2. Based on the estimate assuming 3 cycles, the sample size was calculated as 13 (random model) by using R 4.0 software [33–35]. Considering the 20% of lost follow-up rate, we set the sample size as 17.

### Randomization, blinding, and treatment allocation

We mark the intervention (MBYD) as A and the control (placebo) as B. Then, each cycle can be recorded as AB or BA. The clinical research associate (REA) uses SPSS 26.0 to set a random seed and generate adequate random numbers in the range of (0,10) intervals, and all the random numbers will be rounded down. Each generated odd number is regarded as AB and an even number is regarded as BA. The first to third digits are allotted to the first participant, the fourth to sixth digits are allotted to the second participant, and so on. For example, if a series of random numbers generated by a computer is “453728…”, then the first three numbers “453” are given to the first participant and thus the corresponding order of the trial for him/her is “BA-AB-AB” and homoplastically, the next three numbers “728” are given to the second participant and the corresponding order of the trial for him/her is “AB-BA-BA”, and so on.

The allocation result will be written and put into an opaque and sealed envelope that will not be opened until the end of the trials. The granule storage and distribution will be in charge of the REA. Participants and investigators will both be blinded until the end of the trials.

In our experience, MBYD is usually mild and fewer side effects. In the case of SAEs related to MBYD, the supervisor and primary researchers shall decide whether emergency blind breaking is necessary, in order to know what kind of medicine the patient is taking in time. When breaking the blind, researchers should write the date, the reason for opening the blind, and sign on the envelope.

### Data management and monitoring

In the trials, researchers will record and collect all data on the CRFs. The collecting data will be input using EpiData 3.0(EpiData Association, Odense, Denmark). To guarantee the accuracy and completeness of the data, double data input and proofreading will be carried out by two independent researchers. The individual data of the participants and the data generated during the study will be kept confidential by one researcher, and the result report after the study will not reveal the personal identity of the participants. the State Food and Drug Administration, the Ethics Committee, investigator, and sponsor representatives will be allowed access to participant data in order to verify clinical study procedures and/or data. We will do everything within existing laws to protect the privacy of our participants. A data monitoring plan will be formulated and the study data will be monitored by independent data monitors. All adverse events of the participants will be recorded in detail, properly handled, and tracked until the conditions are properly resolved or stabilized, and SAEs and unexpected events will be reported to the Ethics Committee, competent authorities, sponsors and drug regulatory authorities in a timely manner as required; The primary residents periodically conducted cumulative reviews of all adverse events, and convened investigator meetings when necessary to assess the risks and benefits of the study.

### Follow-up after the trial

Patients who have finished all the cycles will be invited to the research center to follow up after 1 month, researchers will evaluate QMG, TCM syndrome scale, MGC,MG-QOL,MG-ADL and the safety assessments. If the patient’s result report reveals MBYD is beneficial to treat MG, we would give him/her a suggestion that MBYD can be used as an adjunct medicine with the conventional western medicine to alleviate muscle weakness symptoms and enhance the quality of life.

### Statistical methods

MG is a rare disease with high heterogeneity among patients. Bayesian analysis methods will be used to analyze the efficacy of MBYD in treating MG in individuals and populations. Hierarchical Bayesian statistical method is on account of the Monte Carlo technology of Markov’s Bayesian hierarchical model calculation chain, using WinBUGS software for calculation. To combine the results of the multiple N-of-1 trials, a hierarchical model will be used to analyze the difference in efficacy under stratification. The confounding variables such as TCM syndrome differentiation and the potential carryover effect of TCM will be used as the structural grouping factors (or the levels of the model). Suppose there is a common internal residual in the trials. For this multistage model, the trials will use a Bayesian approach to combine data from individual N-of-1 trials. We have elicited a prior distribution for the mean difference effect: a normal distribution with mean 3.00 and a SD of 1.94 [36]. Hence, we will acquire marginal posterior distribution for the mean treatment effects at the population levels and for the variations between patients, as well as a posterior distribution of treatment effects at the individual level, which will exhibit borrowed power through contraction from the population estimates to the population mean. For more details about the program used, see Zucker et al. (2006, especially the appendix) [37]. The probability distributions of each model will be analyzed to assess violations and data transformations undertaken, where necessary. Conventional burn-in periods, model convergence and stability diagnostics as well as residual checks will be adopted. The patterns of hierarchical Bayesian statistics analysis results will be as follows: (1) the mean of the posterior distribution of the mean difference between the outcomes of MBYD and placebo, which provides the best evaluation of the difference in the overall effect size between the treatments; (2) the relevant 95% credible region, which gives uncertainty interval of the posterior distribution (2.5 and 97.5 percentiles in this case), and (3) the posterior probability of mean difference that MBYD will be better than the placebo, which describes the likelihood that the patients will squint towards actively treat in future cycles. At the time that these estimated values are better than predetermined threshold values (e.g., the increment of the average of QMG score is ≥3 points), the patient will be defined as a “responder” [33, 38, 39].

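### The posterior probability that the mean difference favours MBYD is described as a likelihood for patients in future cycles, which needs a posterior predictive probability

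*Protocol article*

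**What the plan says.** Statistical methods announces three results from the hierarchical model: the posterior mean of the difference between MBYD and placebo, its 95% credible interval, and "the posterior probability of mean difference that MBYD will be better than the placebo". The third is given a meaning: "which describes the likelihood that the patients will squint towards actively treat in future cycles".

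The level of the mean difference is not stated outright. The first result is said to be one "which provides the best evaluation of the difference in the overall effect size between the treatments", and the prior placed on the mean difference is "a normal distribution with mean 3.00 and a SD of 1.94"; both point to the population mean. The same section also plans population posteriors "as well as a posterior distribution of treatment effects at the individual level", and the sentence after the three results uses those estimates to classify a single patient as a responder, which blurs the level. The model includes variation between patients and a shared within-patient error ("Suppose there is a common internal residual in the trials"). No predictive probability, for a patient or for a cycle, is mentioned.

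**The concern.** The posterior probability that a mean exceeds zero expresses certainty about an average. If the true mean favours MBYD, it moves towards 1 as patients are added, even when a sizeable share of patients gain nothing. Whether a patient does better on MBYD in a future cycle is a different question. Its answer must also carry the spread of effects between patients and the noise of a single cycle. The model contains both components, but the interpretation attached to the third result uses neither.

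This matters in a plan that stresses high heterogeneity and chose the N-of-1 design for its value to individuals. A near-certain statement about the average, worded as a patient's prospect, would be read as a much stronger promise than the data can support.

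**Working it through.** **Inputs from the article.** Sample size: pilot difference 3.00 with SD 1.94, Ψ = 3.0, two-sided α 0.05, β 0.2, 3 cycles, 13 patients raised to 17. Statistical methods: Normal prior with mean 3.00 and SD 1.94 on the mean difference. Positive values denote benefit.

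**Reproducing the plan's own figure.** The article does not say what Ψ measures. Read it as the between-patient SD of the treatment effect, and 1.94 as the SD of one measurement. The variance of a patient's three-cycle mean difference is then 3.0² + 2 × 1.94²/3 = 11.51. A one-sample t-test for a difference of 3.0 has power 0.796 at n = 12 and 0.833 at n = 13, so n = 13 as stated; 13/0.8 = 16.25, hence 17. If 1.94 is instead taken literally as the SD of a cycle difference, the variance is 9 + 1.94²/3 = 10.25 and n = 12. The first reading reproduces the plan, but it remains an inference. I therefore use a cycle-difference SD s from 1.94 to 1.94 × √2 = 2.74.

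**Method.** Normal hierarchical model with variances treated as known, n = 17:
- sampling variance of the observed mean: V = (Ψ² + s²/3)/17
- posterior variance: v = 1/(1/1.94² + 1/V)
- posterior mean: m = v × (3.00/1.94² + observed mean/V)
- planned result: P(mean > 0) = Φ(m/√v)
- new patient's true effect > 0: Φ(m/√(v + Ψ²))
- new patient's future cycle favours MBYD: Φ(m/√(v + Ψ² + s²))

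**Example.** Ψ = 3.0, s = 2.74, observed mean 2: V = 11.51/17 = 0.677, v = 0.574, m = 2.15. The three probabilities are Φ(2.15/0.757) = 0.998, Φ(2.15/3.09) = 0.757 and Φ(2.15/4.14) = 0.699.

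**Results with Ψ = 3.0** (ranges run over s from 1.94 to 2.74):

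| Observed mean | P(mean > 0) | New patient's effect > 0 | New patient's future cycle > 0 |
|---|---|---|---|
| 3 | 1.000 | 0.834–0.835 | 0.766–0.795 |
| 2 | 0.9978–0.9985 | 0.756–0.757 | 0.699–0.721 |
| 1 | 0.958–0.962 | 0.660–0.663 | 0.624–0.637 |

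The gap between the second and last columns is about 20 to 33 percentage points.

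**Patient-level reading.** Take an enrolled patient whose own three-cycle mean is 3, with the population mean taken as known and equal to 3, and Ψ = 3.0. The posterior variance of that patient's effect is 1/(1/9 + 3/s²) = 1.10 (s = 1.94) or 1.96 (s = 2.74).
- Effect > 0: Φ(3/√1.10) = 0.998, or Φ(3/√1.96) = 0.984.
- Next cycle > 0: Φ(3/√(1.10 + 3.76)) = 0.913, or Φ(3/√(1.96 + 7.53)) = 0.835.

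The gap is about 9 to 15 points.

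**Sensitivity to Ψ.** With Ψ = 0 and an observed mean of 3, the planned figure is 1.000 against 0.937 (s = 1.94) or 0.861 (s = 2.74), a gap of about 6 to 14 points. That narrowing belongs to the large mean. With Ψ = 0, s = 1.94 and an observed mean of 1, m = 1.04 and v = 0.072, and the future-cycle figure is Φ(1.04/√(0.072 + 3.76)) = 0.70 against 0.9999.

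**The case against.** Several points on the other side have force.

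- *The level is not settled.* The article says mean difference, not population mean difference, and the responder sentence is about one patient. This stands. It reduces the gap but does not close it, because a patient's mean effect is still not that patient's next cycle.
- *The sentence is poorly translated.* It may only mean leaning towards active treatment in future, and for that choice the sign of a patient's mean effect is a relevant quantity. That is a fair reading, but the text presents the number as a likelihood concerning patients in future cycles, and a reader will take it so.
- *Nothing formal depends on it.* The estimates and intervals are unaffected, and the only example threshold is 3 QMG points, not a cut-off on this probability. This stands and limits the consequence to interpretation and reporting.
- *The fuller plan may include predictive outputs.* It may, but the point concerns an interpretation that the article does state, not an omission.

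A reader might go further and infer that the population probability will be handed to patients as their own prospect. The documents do not show this. In Follow-up after the trial, the advice depends on whether the individual patient's own "result report reveals MBYD is beneficial to treat MG", and individual posteriors are planned. A reader might also infer that the probability tends to 1 however many patients fail to benefit. It does so only if the true mean favours MBYD; if enough patients worsen, it tends to 0.

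**Conclusion.** The interpretation is wrong as written at either level, and nothing else in the article corrects it. The direction is conditional: the planned figure is too high when the posterior mean favours MBYD, and too low if the mean favours placebo.

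The size is less certain than the error. The gap of 20 to 33 points for a new patient's future cycle assumes that Ψ is an SD of 3.0, that the variances are known and that 17 patients complete three cycles. On the patient-level reading it is about 9 to 15 points at a mean of 3, and at that mean with Ψ near zero about 6 to 14 points for a new patient. It would therefore go too far to call the overstatement large in every case, although the article's own claim of high heterogeneity argues against Ψ near zero. The design, the data and the estimates remain valid; what needs correcting is the meaning attached to one of the three announced results.

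**What to change.** State whether the third result refers to the population or to the patient, label it as the posterior probability that the mean effect favours MBYD, and remove the reference to future cycles from it. From the same WinBUGS model, add posterior predictive probabilities for two quantities: the effect in a new patient, and each enrolled patient's next-cycle difference. Use these for any statement about future cycles.

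The cost is a few lines of model code and revised wording, with no change to design, data collection or sample size. The price in presentation is that, where MBYD is favoured, the probability quoted for future cycles will be less favourable than the one now planned.

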
### Auditing

A research assistant supervises the sequence and procedure of the trial, and this process is independent from the other investigators.

## Discussion

According to our rich clinical experience, we found that TCM treatment can alleviate fatigue and muscle weakness and improve the quality of life of MG patients. A series of N-of-1 trials is currently a helpful tool for maximizing clinical benefits for an individual patient and has significant potential to supply convincing effective information for most clinical fields [40]. It can be seen as conducting multiple RCTs on individuals. TCM is highly consistent with N-of-1 trials because TCM is characterized by syndrome differentiation and holism emphasizing individualized treatment. In recent years, more and more scholars have paid attention to TCM N-of-1 trials.

It is challenging to assess the effectiveness of TCM because of its heterogeneous ingredients, multiple targets, and miscellaneous effects. In this study, we plan to use QMG, MGC, and MG-ADL clinical rating scales to evaluate the severity of MG and MG-QOL for assessing the quality of life in MG patients and the TCM symptom scale for analyzing the syndrome improvement. Meanwhile, the level of Treg cells and related cytokines are also our outcomes so as to comprehensively evaluate the effectiveness of TCM. In addition, the changes of gut microbiota through TCM treatment can also be used as a method to evaluate the effectiveness of TCM. Therefore, we innovated to use multiple crossovers within the N-of-1 trials for detecting and analyzing the composition of gut microbiota, aiming to form credible evidence that the effect of TCM on how to modulate the composition of gut microbiota in MG patients.

For TCM N-of-1 trials, previous studies published or conducted have an inferior reporting quality [41]. On the one hand, because of the multi-target and confounding effect of TCM, it is hard to determine the half-time and onset time, which brings the difficulty to set the period of intervention and wash-out. On the other hand, how to evaluate the clinical effectiveness of TCM still needs to be further improved. Besides, a part of TCM treatments may have a slow onset of clinical effects and do not show curative effects in a short period, which brings some difficulties to the conductions of TCM N-of-1 trials. Nevertheless, TCM N-of-1 trials still have great potential and their future is worth looking forward to.

## Trial status

The recruitment began on 5 Dec 2020, and we expect this study to be completed by 30 May 2022.

## Abbreviations

MG: Myasthenia gravis
QMG: Quantitative myasthenia gravis
TCM: Traditional Chinese medicine
MGC: Myasthenia gravis composite
MG-ADL: Myasthenia gravis activities of daily living profile
MG-QOL: Myasthenia gravis quality of life
BYD: Buzhong Yiqi decoction
MBYD: Modified Buzhong Yiqi decoction
N-of-1: Single-case randomized controlled trial
RCT: Randomized controlled trial
GZUCM: Guangzhou University of Chinese Medicine
CENT: CONSORT extension for reporting N-of-1 trials
CRF: Case report form
AChR: Acetylcholine receptor
Treg cell: Regulatory T cell
INF-γ: Interferon-γ
TGF-β: Transforming growth factor-β
IL: Interleukin
SAE: Serious adverse effect
SD: Standard deviation
REA: Research associate
